The sites delivering gFNP are established FNP sites and gFNP will be delivered in addition to the one to one FNP program in those sites, to clients who would are ineligible for FNP. The program is delivered to each group by two family nurses trained according to US NFP guidelines and who are experienced in delivering home-based FNP [26], one of whom is a practising midwife. Each group comprises between 8 and 12 women, whose partners are encouraged to attend. Women using group based antenatal care such as the Centering Pregnancy Model [27], reported a preference for this approach over traditional care [28-30]. Centering Pregnancy has been associated with improved prenatal outcomes such as reductions in preterm births among high-risk women [31,32]. Following this model of delivery, gFNP provides routine midwifery care in pregnancy and infant health checks according to NICE guidelines [33] during the gFNP session with encouragement for mothers to conduct the necessary pregnancy checks themselves with guidance from the family nurses and midwives. Any out-of-hours antenatal care is managed according to local arrangements (this may involve a community midwifery team or hospital) and intrapartum care is managed by the hospital/birth center midwifery team. The group context should help mothers to develop social networks with other local mothers [34], and to benefit from peer-group learning. Also, meeting in Children’s Centers helps families to become familiar with the other services and to develop regular contact with other professionals when additional support is called for [35].

An implementation evaluation in England found that both the mode of delivery and materials were acceptable to clients and nurses [34-36]. In addition to developing relationships with the family nurses, clients have developed close relationships with group members and made regular use of other services in the Children’s Centers. The delivered content of gFNP is consistent with NFP US National Office recommendations [36] and the prediction is that gFNP is likely to be associated with the same kinds of benefits as the individually delivered program. However, in order to provide optimal information for service providers and commissioners, and to provide the most effective support for potentially vulnerable families, it is important that programs be subject to rigorous randomized trials to provide evidence about efficacy and cost-effectiveness.

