### Sample size

The sample size was calculated for the two primary outcomes, the revised Adult Adolescent Parenting Inventory (AAPI-2) [39] and the observational CARE Index [40-42]. The standard deviation (SD) of the AAPI-2 is 10, with differences of 6.7 identified in the normative sample between abusive and non-abusive adult females [39]. The standard deviation for the CARE Index is expected to be around 2.3 [41].

For this individually randomized trial, we propose to recruit sufficient mothers and babies (families) to allow the trial to detect a difference between groups of 0.5 standard deviations, with 90% power at a significance level of 0.05 (2-tailed); this is considered to represent a moderate size of effect [43]. Basing calculation on the AAPI-2, very conservatively assuming a correlation of 0.4 between pre and post intervention scores we would need at least 71 families in each arm of the trial to detect this difference. Allowing for an expected 30% drop out rate (based on the first two applications of the program in England) we would need to recruit a minimum of 84 families per arm of the trial. We therefore propose, conservatively, to recruit a minimum of 100 families per arm (N = 200). In the intervention arm this will consist of 10 groups of (generally) 10 families (N = 100), with 2 groups provided per site. However, given that the minimum number required for a viable group is 8, 7 sites are involved in the trial so that it will be possible to recruit a minimum of 208 (if one site proves able to deliver only one group of 8) and potentially at least 224 participants (2 groups of 8 per site plus the same number of controls). It was necessary to have two more sites than the five originally proposed to cope with the possibility that in one or more areas area the minimum number of women would not be recruited to form a viable group. The proposed sample size would similarly allow us to detect a change of approximately 0.5 standard deviations in the CARE index [40-42]. We would therefore expect to be able to detect a difference at follow-up between arms of the trial of approximately 1.2 with 90% power and a 5% level of significance.

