### Data analysis

#### Outcomes

Statistical analysis will be carried out at the individual level. Every effort will be made to obtain outcome measures for participants, even if some drop out during the course of the group sessions or move out of the local area so have to stop attending gFNP.

Analyses will be carried out using two different types of dataset:

i) The intention-to-treat datasets: data will be analyzed based on participants according to the random allocation irrespective of whether the intervention was or was not entirely or partly taken up.

ii) The per-protocol datasets: as it is possible that participants may not receive the intervention, the intention-to-treat analysis might underestimate the potential efficacy of intervention. A per-protocol analysis will therefore be carried out in addition to the intention-to-treat analysis. The per-protocol datasets will include data pertaining to all outcomes, restricted to those participants who complied fully or partly with their assigned intervention.

The primary analysis will use the intention-to-treat datasets. Demographic and other characteristics at trial entry will be tabulated using the intention-to-treat datasets. No significance tests will be performed to test for differences at baseline. Descriptive statistics for continuous variables will include the mean, standard deviation, median, range and the number of observations. Categorical variables will be presented as numbers and percentages.

The data will be analyzed by multiple regression modeling, with appropriate generalized linear models (GLMs) used to examine the effect of the intervention, fitting baseline measures of outcomes as covariates, where available. A small number of secondary analyses based on explicit hypotheses, for example, subgroup (including ‘looked after’ history)/explanatory analyses (considering compliance with the interventions) will be specified in advance (in a statistical analysis plan). The secondary analyses will include an analysis in which the small groups in which the intervention is delivered will be fitted as a random effect to allow for any potential clustering by group. Sensitivity analyses will be conducted for all primary outcomes. Inverse probability weighting would be considered if missing data were larger than expected and/or there was differential attrition between the trial arms. Additionally, reasons for the differential attrition will be fully explored.

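### gFNP groups exist in the intervention arm only, yet the model that allows for them is secondary and the sample size carries no design effect; for any positive group ICC the deciding test exceeds 5%

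*Protocol article*

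**What the plan says.** On delivery, the Group Family Nurse Partnership section of the protocol article states: "Each group comprises between 8 and 12 women, whose partners are encouraged to attend". Each group is led by two family nurses. The same section expects benefit to come partly through local social networks and learning from peers. Study design gives 44 sessions over 76 weeks. Under Study setting, controls receive universal midwifery and health visiting services, with no trial groups.

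On size, the Sample size section treats the trial as individually randomized and aims to "detect a difference between groups of 0.5 standard deviations" "with 90% power at a significance level of 0.05 (2-tailed". It arrives at 71 families per arm before dropout and a target of 100 per arm. The base layout is described thus: "In the intervention arm this will consist of 10 groups of (generally) 10 families (N = 100". It then explains that seven sites are used, giving a minimum of 208 participants and potentially at least 224, in groups of 8. It states no ICC and no design effect.

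On analysis, the Outcomes part of Data analysis plans multiple regression or generalized linear models with baseline measures as covariates where available. The delivery group enters only later: "The secondary analyses will include an analysis in which the small groups in which the intervention is delivered will be fitted as a random effect".

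**The concern.** Women in one gFNP group share nurses, peers and over a year of sessions, so some positive correlation of outcomes within groups is plausible; on the protocol's own account of the mechanism it is expected. Randomizing individuals does not remove it, because it arises after allocation. Minimizing by site does not remove it either, because groups within a site can still differ.

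If the correlation is positive, a regression without a group effect understates the variance of the intervention mean. The standard error is too small, the confidence interval too narrow, and the test of no average benefit across groups rejects too often. That null is the relevant one for a program meant for wider delivery. The error runs in one direction, and if the two planned models disagree, the protocol lets the anti-conservative one decide. Power computed for independent women is overstated for the same reason.

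**Working it through.** **Inputs from the protocol (Sample size, and Table 1 for the CARE Index).** Difference 0.5 SD; two-sided 5%; power 90%; baseline to follow-up correlation 0.4 for AAPI-2; loss 30%. Scale: "The standard deviation (SD) of the AAPI-2 is 10" and "The standard deviation for the CARE Index is expected to be around 2.3". Table 1 shows the CARE Index at 12 months only, so it has no baseline covariate. Layouts: 10 groups of 10 (100 per arm); 13 groups of 8 (104 per arm, 208 in all); 14 groups of 8 (112 per arm, 224 in all).

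**Assumption.** ICC 0.01 to 0.10. The protocol gives none.

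**Step 1: reproduce the 71.** Working in SD units, the residual variance after baseline adjustment is 1 − 0.4² = 0.84. Then n = 2 × 0.84 × (1.960 + 1.282)² / 0.5² = 70.6, rounded up to 71. This matches with a design effect of 1, so clustering is absent from the figure. The target leaves no hidden reserve: 100 × 0.7 = 70 evaluable per arm, with AAPI-2 power of 89.8% before any clustering.

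**Step 2: formulas.** With m evaluable women per group, n per arm and k groups in the intervention arm only:

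- Var(difference) = σ² × [2 + (m − 1) × ICC] / n, with σ² = 0.84 for AAPI-2 and 1 for the CARE Index.
- Variance inflation relative to independence: V = [2 + (m − 1) × ICC] / 2.
- Actual type I error of the unclustered test: 2 × [1 − Φ(1.96 / √V)].
- Power of a test with the correct standard error: Φ(0.5 / SE − 1.96).

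Worked case, m = 7, n = 70, ICC 0.05: V = (2 + 0.30)/2 = 1.15. Type I error = 2 × [1 − Φ(1.96/1.072)] = 6.8%. AAPI-2 SE = √(0.84 × 2.30/70) = 0.166, and power = Φ(3.01 − 1.96) = 85.3%.

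**Step 3: results after 30% loss, normal approximation.**

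| Layout | ICC | V | Type I error | AAPI-2 power | CARE power |
|---|---|---|---|---|---|
| 10 groups of 7 (70 per arm) | 0 | 1.00 | 5.0% | 89.8% | 84.1% |
| | 0.01 | 1.03 | 5.3% | 88.9% | 83.0% |
| | 0.02 | 1.06 | 5.7% | 88.0% | 81.9% |
| | 0.05 | 1.15 | 6.8% | 85.3% | 78.8% |
| | 0.10 | 1.30 | 8.6% | 80.8% | 73.7% |
| 13 groups of 5.6 (208 recruited) | 0.01 | 1.02 | 5.3% | 90.2% | 84.7% |
| | 0.05 | 1.12 | 6.3% | 87.6% | 81.5% |
| | 0.10 | 1.23 | 7.7% | 84.3% | 77.6% |
| 14 groups of 5.6 (224 recruited) | 0.01 | 1.02 | 5.3% | 92.2% | 87.2% |
| | 0.05 | 1.12 | 6.3% | 89.9% | 84.2% |
| | 0.10 | 1.23 | 7.7% | 86.9% | 80.6% |

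**Step 4: checks.**

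- Simulated baseline-adjusted regression (20,000 replicates, 10 groups of 7) rejected a true null in 5.1%, 6.0%, 6.5% and 8.7% of trials at ICC 0, 0.02, 0.05 and 0.10, in line with the formula.
- Satterthwaite degrees of freedom lower AAPI-2 power with 10 groups of 7 to 86.8% at ICC 0.01 and 77.3% at 0.10. With 14 groups of 5.6 the figures are 91.0% and 84.9%.

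**Step 5: separate the CARE Index shortfall.** At 70 per arm and 0.5 SD, CARE power is Φ(0.5/√(2/70) − 1.96) = 84.1% with no clustering at all, because the 71 relies on a baseline covariate that CARE lacks. Taking the protocol's difference of 1.2 on an SD of 2.3 (0.52 SD) gives 87.0%. Only the fall below the ICC = 0 value is due to clustering.

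**The case against.** The strongest reply is that the protocol already specifies the better model, so the dispute is about the order of two planned analyses, and that the damage depends on an ICC nobody has stated. Much of this stands.

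- A reader might infer that the plan ignores clustering. It does not; the group random effect is planned. What omits it is the deciding model and the sample size.
- A reader might take "Statistical analysis will be carried out at the individual level" as proof of neglect. It is not: a mixed model with a group effect also analyses individuals.
- A reader might infer that the error certainly exceeds 5%. That needs a positive ICC. At 0.01 to 0.02 the excess is under one percentage point, and no document supports 0.10. Intention-to-treat also keeps women who attended little or nothing, which would dilute the correlation.
- A reader might judge power only by the layout of 10 groups. The seven-site plan softens the loss: with 224 recruited, AAPI-2 power is still 89.9% at ICC 0.05 by normal approximation.
- A reader might attribute the whole CARE deficit to clustering. At 70 per arm and ICC 0.05, 5.9 of the 11.2 points below 90% are there without it.

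What does not fall is the choice itself. Random-effect details can wait for the SAP, but the protocol fixes which model is secondary, and an SAP that follows it inherits the problem.

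**Conclusion.** The point holds in conditional form. The design is partially nested, the protocol makes the unclustered model decisive, and its sample size has a design effect of 1. For any positive group ICC the deciding test is anti-conservative. Over an assumed ICC of 0.01 to 0.10 and 30% loss, the type I error is 5.3% to 8.6% with 10 groups of 7 evaluable, or 5.3% to 7.7% with groups of about 5.6 under the seven-site plan.

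By normal approximation, AAPI-2 power runs from 89% to 81% at 70 per arm, 90% to 84% with 208 recruited and 92% to 87% with 224; small-sample degrees of freedom take off a little more. CARE power at 70 per arm starts at 84% for a different reason, and clustering takes it to between 83% and 74%. At the low end the effect is minor; at the high end it matters for both error rate and power. The documents cannot say where in the range the trial lies.

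**What to change.** In the Outcomes part of Data analysis, make the model with a gFNP-group random effect in the intervention arm only the primary analysis for both primary outcomes, using small-sample degrees of freedom. The SAP can settle the coding of controls, residual variances and the degrees-of-freedom method. Keep the unclustered model as a sensitivity analysis. Make the change before anyone has seen outcomes by arm, since swapping the deciding model later would not be credible.

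In Sample size, restate power for the seven-site plan over a stated ICC range, and give the CARE Index its own figure without baseline adjustment.

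The cost is wording, slightly wider confidence intervals and a lower stated power. With 10 groups of 7, the correct standard error is √1.03 to √1.30 times the naive one, so 1.5% to 14% larger. No more women need be enrolled for the analysis to be valid. Holding 90% AAPI-2 power with 7 evaluable per group would take about 105 to 132 recruits per arm (73/0.7 to 92/0.7), against 104 to 112 under the seven-site plan, so the lower power should simply be stated.

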#### Economic evaluation

A prospective economic evaluation, conducted from an NHS and personal social services perspective, will be integrated into the trial. The economic assessment method will, as far as possible, adhere to the recommendations of the NICE Reference Case [54]. Primary research methods will be followed to estimate the costs of the delivering gFNP, including development and training of accredited providers, the cost of delivering the group sessions, participant monitoring activities, and any follow-up/management. Broader resource utilization will be captured through two principal sources: (i) routine health service data collection systems described above; and (ii) patient questionnaires administered at baseline, two months postpartum, and twelve months postpartum with a telephone contact at six months to minimize loss of information due to recall difficulties. Unit costs for health and social care resources will largely be derived from local and national sources and estimated in line with best practice. Primary research using established accounting methods may also be required to estimate unit costs. Costs will be standardized to current prices where possible.

Maternal health-related quality of life, measured at baseline, two months postpartum, six months postpartum and twelve months postpartum using the EuroQol EQ-5D-5L [51] will be converted into health utilities using established utility algorithms [52] for the purposes of quality-adjusted life year (QALY) estimation. The results of the economic evaluation will primarily be expressed in terms of incremental cost per QALY gained. Non-parametric bootstrap estimation will be used to derive 95% confidence intervals for mean cost differences between the trial groups and to calculate 95% confidence intervals for incremental cost effectiveness ratios [55]. A series of sensitivity analyses will explore the implications of uncertainty on the incremental cost-effectiveness ratios and will consider the broader issue of the generalisability of the results. One such analysis will adopt a societal perspective incorporating direct costs to trial participants and their partners, informal care provided by family and friends, and productivity losses. In the baseline analysis, and for each sensitivity analysis, cost-effectiveness acceptability curves will be constructed using the net benefits approach [56].

More extensive economic modeling using decision-analytic methods will extend the time horizon of the economic evaluation, drawing on best available information from the literature together with stakeholder consultations to supplement the trial data. Parameter uncertainty in the decision-analytic model will be explored using probabilistic sensitivity analysis. Longer term costs and consequences will be discounted to present values using discount rates recommended for health technology appraisal in the United Kingdom [54]. Given the plethora of outcome measures across several domains for the mother, child and broader family, a separate discrete choice experiment (DCE) will be conducted. The possibility of combining the outputs of the DCE with cost estimates and changes in relevant outcomes within a cost-benefit analysis framework will be explored.

#### Process

Characteristics of study participants and those who decline to participate or are ineligible will be identified (demographic and risk profiles) and contrasted with those of the wider population in the study areas. The representativeness of recruited families will be assessed by analyzing anonymized data for each expectant woman approached: age; parity; any risk factors collected during routine booking-in (for example, history of mental health problems); in relation to their acceptance or rejection of the agreement for researcher contact.

The uptake rate of women who agree to the intervention will involve an assessment of the ratio of women randomized to receive the intervention who then attend at least one session relative to those who either refuse after meeting with the family nurse, or who agree but never attend any sessions. The study attrition rate will be estimated in terms of the proportion of women who drop out relative to those who continue in either arm of the trial and also those who may or may not take part in research visits but cease to receive the intervention, based on information provided by the nurses delivering the program. The extent to which the program is being delivered with integrity will be assessed though analysis of data from the program’s standardized data forms documenting attendance, the content domains covered in each session and participants’ responses to the content, comparing the information with recommendations for delivery from the US NFP National Office and from the UK FNP National Unit.

All qualitative interviews will be transcribed and analyzed thematically [57]. Interviews with women and their partners with a looked-after history will be analyzed using a computer-aided qualitative data analysis package informed by interpretive phenomenology which seeks to represent the experiences of the research participants in context [58].

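### Uptake is defined as a ratio of attenders to some non-attenders, not over all women randomized to gFNP, and the attrition wording is ambiguous

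*Protocol article*

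**What the plan says.** All of the definitions are in the protocol article, Data analysis, under Process.

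- **Uptake** is to be assessed through "the ratio of women randomized to receive the intervention who then attend at least one session" set "relative to those who either refuse after meeting with the family nurse, or who agree but never attend any sessions". The sentence introduces this as the uptake rate of women who agree to the intervention.
- **Attrition**: "The study attrition rate will be estimated in terms of the proportion of women who drop out relative to those who continue". This covers both arms. The same sentence then adds "also those who may or may not take part in research visits but cease to receive the intervention", with the nurses who deliver the programme as the source of that information.

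Three other places bear on how these figures will be read.

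- The Recruitment section has each woman randomized individually after her baseline visit. She learns her allocation by post, and the FNP team is told by fax. There is therefore an interval between randomization and the first meeting with a nurse.
- The Sample size section plans "to recruit a minimum of 100 families per arm (N = 200"), and reaches its target by "Allowing for an expected 30% drop out rate (based on the first two applications of the program in England").
- The Outcomes part of the data analysis section says that inverse probability weighting would be considered "if missing data were larger than expected and/or there was differential attrition between the trial arms".

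**The concern.** A reader expects an uptake rate to be the share of women allocated to gFNP who attended at all. The stated rule has attenders on top and only two named groups of non-attenders beneath. That is an odds, and the two groups do not exhaust the women who never attend. A woman who opens the letter and declines at once, or whom the team never reaches, has neither refused after meeting a nurse nor agreed and stayed away. She drops out of the calculation.

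The attrition sentence calls its measure a proportion but sets dropouts against continuers. It also places women who stop the programme under the study attrition label, and only gFNP women can stop the programme.

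Uptake and retention are what commissioners will use to judge whether a null result reflects the programme itself or its non-receipt. A flattering uptake figure points them towards the first explanation. An attrition figure that could sit on either of two scales cannot safely be set beside the planning value or compared between arms.

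**Working it through.** The article gives no numerical uptake or attrition result, so there is no stated figure to reproduce. The check puts numbers into the definitions.

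**Inputs from the document:** 100 women per arm and 30% expected dropout (Sample size); the uptake and attrition wording (Process).

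**Assumed for illustration:** the number of gFNP women who attend, and the number lost before meeting a nurse. The article gives neither, so a range is shown.

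**1. Uptake.** Let N be the women randomized to gFNP, A those attending at least one session, and b those who decline or cannot be reached before meeting a nurse.

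- As worded: A / (N − A − b)
- The same counts turned into a proportion: A / (N − b)
- Over all randomized: A / N

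With N = 100:

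| A | b | As worded | As a proportion of women counted | Over all randomized |
|---|---|---|---|---|
| 60 | 0 | 60/40 = 1.50 | 60.0% | 60% |
| 60 | 5 | 60/35 = 1.71 | 63.2% | 60% |
| 60 | 10 | 60/30 = 2.00 | 66.7% | 60% |
| 70 | 0 | 70/30 = 2.33 | 70.0% | 70% |
| 70 | 5 | 70/25 = 2.80 | 73.7% | 70% |
| 70 | 10 | 70/20 = 3.50 | 77.8% | 70% |
| 80 | 0 | 80/20 = 4.00 | 80.0% | 80% |
| 80 | 5 | 80/15 = 5.33 | 84.2% | 80% |
| 80 | 10 | 80/10 = 8.00 | 88.9% | 80% |

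Because N − b is never larger than N, A / (N − b) is never smaller than A / N. The omission can only raise the figure. Converting the odds to a proportion does not remove the error unless b = 0.

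**2. Attrition scale.** Let d be the share of randomized women who drop out. The ordinary proportion is d. Read literally, dropouts relative to continuers is d / (1 − d).

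| d | d / (1 − d) |
|---|---|
| 10% | 11% |
| 20% | 25% |
| 30% | 30/70 = 43% |
| 40% | 67% |
| 50% | 100% |

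**3. Attrition content.** This step applies only if women who stop the programme are counted in the same figure as women lost from the study. Assume 20 of 100 have no outcome in each arm, and a further 15 gFNP women stop sessions but complete their research visits. The merged figure is (20 + 15)/100 = 35% for gFNP against 20/100 = 20% for control. On the literal scale it is 35/65 = 54% against 20/80 = 25%. The true difference in missing outcomes is zero.

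**The case against.** The strongest reply is that these are loosely worded sentences about descriptive process measures in a journal article, and that the alarming numbers come from reading them literally. Much of that stands, and it rules out several stronger conclusions that a reader might draw.

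- **That a 30% dropout would be reported as 43%.** The sentence calls the measure a proportion, and the Sample size section uses dropout rate in its ordinary sense. The authors may well intend a plain percentage of those randomized. The 43% shows what the wording permits; the article nowhere states it.
- **That programme stopping is merged into study loss.** The added clause names a distinct group with its own data source, so it may be a second quantity reported alongside the first. The Outcomes section separates the two ideas, since outcomes are to be sought from women who leave the group sessions. What remains is that one label is used for both.
- **That this measure would trigger inverse probability weighting.** The Outcomes section speaks of missing data and differential attrition but does not tie either to the Process definition.
- **That women who lose the pregnancy, or whose group never forms, are left out of uptake.** If they had agreed, they fall among those who agree but never attend. Only women who decline or cannot be reached before meeting a nurse are clearly outside.

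It can also be said that the uptake sentence announces a restricted scope, women who agree, and describes an assessment, not a closed formula. This helps less. The comparator includes women who refuse, so the scope and the rule do not match. Stretching agreement to mean consent to the trial would bring in every non-attender, but it would also make the separate category of refusal after meeting the nurse redundant.

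**Conclusion.** The point holds for uptake. As written, the rule is an odds, and it omits women lost between postal notification and the first nurse contact. The direction of the error is certain: reported uptake is too favourable whenever any such women exist. Its size depends on how many there are, which the article does not say. With 70 of 100 attending, omitting 5 or 10 women gives 73.7% or 77.8% in place of 70%, even after converting the ratio to a proportion.

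For attrition the finding is ambiguity, not a demonstrated error. The same data give 30% or 43% depending on the reading, and a single label serves both loss from the study and stopping the programme.

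The consequence is limited to process reporting and interpretation. A reader might infer that the trial's main result is at risk. It is not: the primary analysis is by intention to treat, and these definitions do not enter it.

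**What to change.** Replace the two definitions with three quantities, each over all women randomized to the arm:

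1. **Uptake**: attended at least one session / all randomized to gFNP, with reasons for non-attendance tabulated, including refusal or no contact before meeting a nurse.
2. **Programme discontinuation**: started and then stopped / all randomized to gFNP.
3. **Study attrition**: no 12-month primary outcome / all randomized, by arm.

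Use the third quantity when judging missing data and differential attrition under the Outcomes section. Because the 30% allowance is drawn from earlier deliveries of the programme, and may therefore describe leaving the programme, say which quantity it is meant to match before comparing the two.

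The change is one of wording. The counts come from the session attendance forms, the allocation records and the follow-up visits already planned. Reasons for non-contact before the first meeting may need a short log by the FNP team if none is kept; the article does not say. The one drawback is that reported uptake may look less favourable.
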